### Mediating variables

#### Social support for eating and exercise

This questionnaire asks respondents to rate on a five point scale (1 = never, 5 = very often) how often friends and family have done or said certain things related to the respondents’ efforts to change their dietary or exercise habits. Social support for eating habits is measured using two five-item subscales (encouragement and discouragement), each calculated separately for friends and family. Internal consistency coefficients range from 0.73 to 0.87. Social support for exercise is measured using one 10-item scale, also calculated separately for family and friends [41].

#### Self-efficacy for eating and exercise behaviors

The Physical Activity and Nutrition Self-Efficacy scale is an 11-item instrument that assesses the participant’s level of confidence that she can complete particular activities that promote weight loss [42]. This scale has adequate reliability, internal consistency, and construct validity, as well as good predictive validity among African-Americans.

#### Perceived access to healthy eating and exercise

These items come from the Robert Woods Johnson Active Where study [43]. Respondents rate their level of agreement (from 1 = strongly agree to 4 = strongly disagree) to four statements related to access to physical activity resources, five statements related to healthy eating resources, and five statements about perceived neighborhood safety. All scales show good internal consistency, with Cronbach’s alphas from 0.78 to 0.94 [43].

### Outcomes

#### Weight outcomes

##### Body Mass Index (BMI)

Height (baseline only) is measured to the nearest 0.1 cm using a portable stadiometer (Seca). Weight is measured to the nearest 0.1 kg using a digital scale (Tanita), with participants wearing light clothes without shoes. Two measurements for height and weight are taken. If there is a discrepancy of more than 0.5 cm for height or 0.2 kg for weight between the first and second measurements, a third measurement is taken. The mean of the two most closely aligned measurements is used to calculate BMI (weight (kg)/height (m)^2^.

##### Waist to hip ratio

Is measured with participants standing without outer garments and with empty pockets. Waist is measured to the nearest 0.1 cm at the level midway between the lower rib margin and the iliac crest, with the participant breathing out gently. Hip is recorded as the maximum circumference over the buttocks. Two measurements are taken. If there is a discrepancy of more than 1 cm, a third measurement is taken. The mean of the two measurements most closely aligned is used for analyses.

##### Body composition: Dual Energy X-ray Absorptiometry (DXA)

DXA allows quantification of the amount of adipose tissue located within the abdominal area and also throughout the entire body of each participant. DXA provides precise, non-invasive measures of fat mass and lean tissue mass (total body, as well as regional) [44]. This method is rapid, requires minimal effort from study participants and compares favorably with hydrostatic weighing for measurement of body fat percentages [45]. DXA measurements of participants’ total and regional fat and lean mass is conducted using the DXA Hologic 4500 W elite.

#### Behavioral outcomes

##### Diet

Our goal is to determine group means for consumption of energy, fruits and vegetables, fat, and fiber. A semi-quantitative Food Frequency Questionnaire (FFQ) is the most appropriate tool in this case [46–48]. The Block 2005 FFQ [49] estimates the usual intake of a wide array of nutrients and food groups, and allows for calculation of the Healthy Eating Index (HEI). Reliability and validity are established for the measure in a wide range of age, gender, income, and ethnic groups [50, 51].

#### Physical activity (self-report and objective)

##### Modified activity questionnaire

Kriska and Caspersen [52] The Modified Activity Questionnaire assesses self-reported leisure activity and television viewing. For leisure activity, respondents review a list of 17 popular activities (e.g., walking, gardening) and select those that they performed on at least 10 occasions in the last year. Participants are also given an opportunity to report leisure activities that are not on the list. Respondents then provide information on average frequency and duration for each activity. Responses are used to calculate the number of hours/week the participant engages in moderate and vigorous activity, along with total MET-hours per week. The questionnaire also asks how many hours per day the participant usually spends watching television. This activity questionnaire has been used in many large studies with diverse samples, including cancer survivors [53], and has well-established reliability and validity [52].

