**Methods/Design:**

Moving Forward is a weight loss intervention being evaluated in a randomized trial with a projected sample of 240 African American breast cancer survivors. Outcomes include body mass index, body composition, waist:hip ratio, and behavioral, psychosocial and physiological measures. Survivors are randomized to either a 6-month guided weight loss intervention that involves twice weekly classes and text messaging or a self-guided weight loss intervention based on the same materials offered in the guided program. The guided intervention is being conducted in partnership with the Chicago Park District at park facilities in predominantly African-American neighborhoods in Chicago. Recruitment strategies include direct contact to women identified in hospital cancer registries, as well as community-based efforts. Data collection occurs at baseline, post-intervention (6 months) and at a 12-month follow-up.

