### Procedures

Women who respond to recruitment efforts complete a brief telephone interview to verify eligibility. Next, confirmation of stage I, II, or III breast cancer and approval for participation in a weight loss program that includes moderate physical activity is sought from the participant’s primary care physician (PCP) and/or oncologist. Once eligibility is established, participants are asked to come in for an interview and physical assessment. At the beginning of this appointment, staff meets individually with each participant to obtain written informed consent. They then complete a 75-min in person interview, a blood draw, blood pressure measurement, dual energy x-ray (DXA), and height and weight measurements. All participants are also asked to wear an accelerometer for 7 days during waking hours. Participants receive a $20 incentive for the interview, $10 for the blood draw, $10 for the DXA and $10 for wearing the accelerometer. Subsequently, participants are randomly assigned to one of two 6-month interventions: (1) Moving Forward guided weight loss intervention (MFG) or (2) Moving Forward self-guided weight loss intervention (SG). Participants once again complete the entire assessment process post-intervention and at a 12-month follow-up.

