#### Moving Forward Guided Program Structure (MFG)

The MFG program meets twice a week for 26 weeks (see Table 1 for weekly themes) and is led by a team that includes a community dietitian, a community cancer exercise instructor, and a health psychologist. The program is conducted in city park district facilities, where participants enjoy free memberships, ongoing access to classes and fitness rooms, and the opportunity to maintain contact with program participants once the program concludes. The first meeting each week includes a 60-min class that addresses knowledge (e.g., relationship between obesity and breast cancer; food label reading; portions; available healthy living community resources), attitudes (e.g., pros and cons of weight loss; understanding the roles that food plays in one’s life; the concept of “fail to plan, plan to fail”) and cognitive behavioral strategies including self-monitoring of weight, food and physical activity; realistic goal setting; stimulus control; problem solving; mindfulness; cognitive restructuring and relapse prevention. These classes are led by a dietitian, a psychologist and a certified cancer exercise trainer. Table 1 provides a list of weekly curriculum topics. Pilot data showed that many women entered the program with low levels of knowledge about healthy eating and exercise. Thus, the first weeks are devoted to teaching core concepts (e.g., concept of calories in/out, food label reading, measuring heart rate), while later weeks are focused on cognitive-behavioral aspects of weight loss such as stimulus control, habit and mindfulness. Class activities include weighing in weekly; completing a food and activity self-monitoring record; increasing awareness of portions by weighing and measuring foods according to one’s typical portions and then according to recommended portions; creating stimulus control plans for home, car and work; identifying barriers to healthy eating and/or exercise and problem solving within small groups; going on a field trip to a local grocery store to practice reading food labels; creating an eating-out management plan; and identifying high-risk situations and brainstorming ways to manage them. The first weekly meeting also includes a support “icebreaker” (share the funniest moment of your breast cancer journey; what has been the most frustrating; etc.) and a 60-min exercise class taught by a certified cancer exercise trainer.

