### Randomization

Approximately one week before the intervention begins at each site, women who completed the baseline visit are randomized in a single block. The allocation assignments for each site are generated using a SAS program written by the data analyst, who has no contact with participants.

A few participants may be unable to complete the baseline visit before the main randomization round. In these cases, the data analyst prepares sealed, numbered envelopes containing the next allocation assignments for the site. As each woman completes her baseline visit, she is assigned the next envelope in the series.

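### The one-year activity window of the Modified Activity Questionnaire lies about half before randomisation at the 6-month visit, so its 6-month leisure score is not a clean post-randomisation outcome

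*Protocol article*

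**What the plan says.** Under Modified activity questionnaire (protocol article, Behavioral outcomes), women review a list of leisure activities and "select those that they performed on at least 10 occasions in the last year". The next step is described without a time frame: "Respondents then provide information on average frequency and duration for each activity". Then "Responses are used to calculate the number of hours/week the participant engages in moderate and vigorous activity", together with total MET-hours per week. A separate item asks "how many hours per day the participant usually spends watching television".

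The timing comes from four other places:
- Abstract, Methods/Design: "Data collection occurs at baseline, post-intervention (6 months) and at a 12-month follow-up".
- Procedures: "Participants once again complete the entire assessment process post-intervention and at a 12-month follow-up". No different recall period is given for the follow-up visits.
- Moving Forward Guided Program Structure: "The MFG program meets twice a week for 26 weeks".
- Randomization: "Approximately one week before the intervention begins at each site, women who completed the baseline visit are randomized in a single block".

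Two other activity measures are collected. The Godin questionnaire refers to a typical 7-day period, and the accelerometer is worn for seven days. Under Data analysis, the two-time-point analysis compares the groups on change from baseline to 6 months, and the three-time-point analysis compares trajectories. Better physical activity patterns are part of the stated hypothesis.

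**The concern.** A window of one year does not fit a visit six months after randomisation. Weeks before randomisation cannot carry a treatment effect, yet they enter the 6-month score, and the same weeks were already counted in the baseline score. Two consequences follow for the MAQ leisure score.

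First, the baseline-to-6-month contrast, which is the plan's two-time-point analysis, is likely pulled toward no difference.

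Second, by 12 months the window lies wholly after randomisation. The group difference can then seem to grow between 6 and 12 months only because the untreated weeks have dropped out of the window. In a trajectory analysis that could be read as continued improvement.

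The article gives no rule for reading a weak 6-month MAQ result beside the accelerometer or the Godin score.

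**Working it through.** **Inputs.** Window 52 weeks (Modified activity questionnaire); visits at 0, 6 and 12 months (Abstract, Procedures); programme 26 weeks (Guided Program Structure); randomisation about 1 week earlier (Randomization); gradual build-up to at least 180 min/week (Intervention goals); N = 240, effect size 0.4, power 0.8, two-tailed, about 10 % attrition at each time point, correlation 0.4 (Power computations). Assumed because not stated: alpha 0.05 and 1:1 allocation.

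**The plan's own figure.** Two-sample comparison, effect 0.4 SD, power 0.8: 99 per arm, 198 in total. Two losses of 10 % leave 0.9 × 0.9 = 0.81, and 198/0.81 ≈ 245, against the stated 240. In reverse, 240 × 0.81 ≈ 194 women give power of about 0.80. The figure is reproduced closely. It is not tied to the MAQ, and the plan states no figure for dilution of this score.

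**Share of the window.**
- Visit 26 weeks after the programme starts: 26/52 = 50 % of the window falls within the programme.
- Counted from randomisation: 27/52 = 52 % is after it, so 25/52 = 48 % is before it.
- Together: about 48–50 % before randomisation.
- If the visit falls 24 to 30 weeks after the start, the programme share runs from 24/52 = 46 % to 30/52 = 58 %.
- At 12 months the window is wholly after randomisation (52/52).

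**Retained effect at 6 months** (scored difference ÷ true difference).
- Frequency averaged over the year, constant effect: 26/52 = 0.50. A true 2 h/week difference is scored as 2 × 26/52 = 1.0 h/week.
- Frequency averaged over the year, linear build-up: the mean over the programme is half the final level, so 0.5 × 26/52 = 0.25 of the end-of-programme difference. For example, a final difference of 180 min/week is scored as 180 × 0.5 × 0.5 = 45. Half of this loss comes from the build-up itself; a window covering only the programme would show 0.5 of the final level.
- Frequency reported only for the weeks when the activity was done: a newly started activity is not diluted, so 1.0.

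**Power, illustrative** (noncentral t, 108 per arm = 216 women after one 10 % loss, true effect 0.40 SD).

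*Effect halved, SD and correlation 0.4 left unchanged:*

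| Analysis | d = 0.40 | d = 0.20 |
|---|---|---|
| Gain score, SD √(2(1 − 0.4)) = √1.2 | 0.76 | 0.27 |
| Baseline-adjusted, SD √(1 − 0.4²) = √0.84 | 0.89 | 0.36 |
| Follow-up only, SD 1 | 0.83 | 0.31 |

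*Overlap modelled explicitly.* Let H1, H2, H3 be successive half-years with unit variance. Baseline = (H1 + H2)/2, the 6-month score = (H2 + H3)/2, and the gain = (H3 − H1)/2. The effect is 0.20. There is no recall error.
- All correlations 0.4: gain variance = 2(1 − 0.4)/4 = 0.30, and 0.20/√0.30 = 0.365, the same as 0.40/√1.2. Gain-score power is 0.76, so nothing is lost. Baseline-adjusted: score variance 0.70, covariance 0.55, r = 0.79, power 0.81 against 0.89 without overlap.
- Correlations 0.4 and 0.16: gain variance = 2(1 − 0.16)/4 = 0.42, and 0.20/√0.42 = 0.309, power 0.62. Baseline-adjusted (r = 0.70): power 0.69.

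So the share of the window is firm, the size of the dilution depends on how frequency is reported, and the power loss depends in addition on SD, correlation and recall error.

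**The case against.** The strongest reply is that the questionnaire section ties the year only to the selection of activities. Frequency and duration follow with no averaging period, so women may report the weeks in which they were active, and a new activity would then lose nothing. The 10-occasion screen does no harm either, since twice-weekly classes over 26 weeks give about 52 occasions. This stands, and it is why the halving is conditional. It does not rescue the score: on that reading an activity dropped since randomisation would still count in full, so the score still would not describe activity after randomisation.

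A second reply is that overlap shrinks the SD of change as well as the effect. This also stands. A reader might infer from the first table that power falls to about 0.27; the documents do not support that as a finding, because it holds SD and correlation at values that overlapping averages would not have. Shrinkage of the SD protects power, but the difference in hours per week remains too small.

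Third, the trial does not depend on this score. The Godin questionnaire and accelerometer describe current activity, the television item asks about usual viewing, and BMI, body composition and waist:hip ratio are untouched. That is correct and limits the point to one score.

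Fourth, a reader might infer that the 12-month contrast is invalid too. It is not: its window is wholly after randomisation. It averages the programme and maintenance periods, so it cannot isolate maintenance.

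**Conclusion.** The point holds for the MAQ leisure score at 6 months. As written, about 48–50 % of its activity window precedes randomisation and overlaps baseline, so the score is not a clean post-randomisation measure and the baseline-to-6-month difference is likely biased toward no effect. About half the true difference is retained if frequency is averaged over the year and the effect is constant; the plan supplies neither condition, and the plausible range is about 0.25 (of the end-of-programme difference) to 1.0. Power loss could be none or large. A rise from 6 to 12 months in this score should not be read as continued improvement. A stronger reading, that the trial's self-reported activity outcome as a whole is halved, is not supported: the Godin questionnaire is also self-report and has a 7-day frame. The sample size and weight outcomes are not in question.

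**What to change.** Either of two changes is enough.

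1. Rest the 6-month activity conclusion on the accelerometer and the Godin questionnaire. Label the 6-month MAQ leisure score as overlapping baseline, and do not use it as a 6-month efficacy outcome. Both replacement measures are already collected, so the cost is only the loss of this score as a 6-month outcome.
2. At the follow-up visits, set the MAQ recall and averaging period to the time since the previous study visit, scale the 10-occasion screen to match, and analyse with baseline as a covariate rather than as change. The cost is a departure from the validated wording and follow-up windows that differ from baseline, though equally in both arms.

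The first is simpler and leaves the form intact. If the 12-month MAQ score is kept with its one-year window, describe it as the average over the programme and the months after it.

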##### Godin leisure-time exercise questionnaire

This brief questionnaire asks how many times in a typical 7-day period the participant performs strenuous, moderate, or mild exercise for more than 15 min during her free time. These responses are used to calculate a leisure activity score and to classify the respondent as active, moderately active, or insufficiently active [54].

##### Accelerometer

The limitations of self-reported physical activity are well established [55]. Therefore, the ActiGraph GT3X activity monitor is used to obtain an objective measure of physical activity. The ActiGraph is a small, lightweight accelerometer designed to detect normal body motion. Participants are asked to wear the ActiGraph during waking hours for seven days. Only days on which the participant wore the accelerometers at least 10 h are included, and participants with fewer than four valid days are excluded from analyses. Thresholds suggested by Troiano and colleagues will be used to calculate the amount of time spent in moderate and vigorous physical activity [56, 57].

#### Biological/physiological outcomes

##### Biomarkers of breast cancer recurrence risk

A fasting blood sample is drawn according to standard procedures by a clinical research center phlebotomist. We chose markers for three proposed mechanisms by which obesity may contribute to breast cancer progression: altering levels of sex hormones (markers: estradiol, estrogen, sex hormone-binding globulin, testosterone), hyperinsulinemia (markers: IGF-I, IGBP3, C-peptide), and chronic inflammation (marker: C-reactive protein, IL-6) [58]. Staff at the clinical research center processes the blood samples according to standard procedures for storage. Briefly, a total of 30 ml of blood is collected in red top vacutainer tubes (without anticoagulant). Blood (approximately 15 ml) is allowed to clot for 20 min and subsequently centrifuged at 2500 rpm for 20 min to separate serum. Staff collects, aliquots serum, which is frozen at-80 °C until analysis. All breast cancer biomarkers are measured using commercially available ELISA kits (R&D Systems and Alpco). Each sample is assayed in duplicate and repeated if variability exceeds 15 %. We will monitor quality control of laboratory tests by ensuring internal positive and negative controls are within the parameters of the test kit for each assay and by evaluating for trends over time.

##### Biomarkers of Co-morbidities

Some of the collected blood is used to examine lipid profiles (HDL, LDL, triglycerides) as a marker of dyslipidemia and Hemoglobin A1c as a marker of impaired glucose tolerance. Individuals with an A1c level at or above 6.5 % who do not report a history of diabetes are informed of the result, provided counseling, and encouraged to follow up with their primary care providers. Hypertension is assessed by measuring diastolic and systolic blood pressure with an OMRON IntelliSense blood pressure monitor using a standard protocol.

#### Psychosocial outcomes

##### Quality of life

The patient-reported outcomes measurement information system (PROMIS) Global Health measure [59] consists of 10 self-reported global health items selected as an efficient way to gather general perceptions of health. The PROMIS items assess 5 domains: physical function, pain, fatigue, emotional distress, and social health. Two dimensions representing physical and mental health underlie the global health items in PROMIS. These global health scales can be used to efficiently summarize physical and mental health in patient–oriented studies.

##### Fatigue

The Brief Fatigue Inventory is a reliable nine-item instrument that uses 0–10 numeric rating scales to evaluate severity of fatigue. A global fatigue score is calculated by taking the mean of the 9 items [60].

##### Symptom checklist

The Breast Cancer Symptom Checklist (BCSCL) was originally developed for the Breast Cancer Prevention Trial and has been validated with a variety of breast cancer populations, including survivors [61]. Respondents are asked if they have experienced any of 17 listed symptoms and then rate the severity on a 5-point Likert-type scale from 0 (not at all bothered) to 4 (extremely bothered). This measure provides scale scores for eight clusters of symptoms: cognitive/mood symptoms, musculoskeletal pain, vasomotor symptoms, nausea, sexual problems, bladder problems, arm problems and body image. We modified the measure and did not include the nausea and sexual problems scales based on advisory board feedback.

### Intervention

Participants are randomized to either the Moving Forward Guided program (MFG) or the Moving Forward Self-Guided program (SG) for six months. MFG includes in-person classes and text messaging, while the SG includes a curriculum manual with handouts related to the intervention topics, but no classes or text messaging.

